### Trial organisation and monitoring

The BEEP trial is sponsored by Keele University. The day to day operation of the trial will be overseen by a Trial Management Group (led by NEF) and the trial will be monitored by an independent Trial Steering Committee (TSC), chaired by [name]. The TSC will be made up of individuals with expertise in musculoskeletal research, exercise physiology and rheumatology. The committee will include two lay members with osteoarthritis. An independent Data Monitoring Committee (DMC) will also monitor the study, chaired by [name]. Terms of reference for the DMC and TSC are available on request from the BEEP trial team. During the trial period through to 18 months follow-up, no interim analyses are planned, unless judged necessary by the DMC. The TSC, DMC, Trial Management Group and clinical partners will remain ignorant of the trial results until the 18 month follow-up data time-point.

### Data confidentiality and archiving

All trial-related information will be stored securely at the Arthritis Research UK Primary Care Centre at Keele University. Data will be anonymised using coded identification numbers to depersonalise data with the housing of the data and the linking code in separate locations, under password protection. Access to the data will be to the small number of individuals necessary for quality control, audit and analysis. The final trial dataset will be accessed by the statistician and the trial principal investigator (NEF). We will publish and communicate the trial results regardless of the outcome of the trial. Data from the BEEP trial will be archived and made available for future, secondary analysis and data pooling purposes from the Arthritis Research UK Primary Care Centre at Keele University.

### Ethical review

The trial received research ethical approved by the North West 1 Research Ethics Committee, Cheshire, UK (REC reference: 10/H1017/45) and site-specific approvals have been received from the appropriate local research and development offices, and we will provide annual reports of progress. The trial is being conducted in accordance with the ethical principles in the Declaration of Helsinki and good practice guidelines on the proper conduct of research.

## Discussion

The BEEP trial will compare the clinical and cost-effectiveness of three physiotherapist-led, exercise-based interventions, for older adults with knee pain attributable to OA in primary care. In comparison to existing trials of exercise for knee OA, the strengths of the BEEP trial are its size, long-term follow-up, and inclusion of a cost-effectiveness analysis and longitudinal qualitative interviews with participants. The main limitation, common to many trials of non-pharmacological interventions, is the inability to blind participants to treatment allocation.

The BEEP trial will inform GPs, physiotherapists, NHS managers and service commissioners about how to optimise the primary care management of older adults with knee pain and about the resources needed to achieve it. It will directly inform this patient group how to optimise the benefits from exercise, inform Primary Care and physiotherapy services about the effectiveness of their management of knee pain in older adults and inform future education of healthcare practitioners. It may also help to delay and prevent some individuals from becoming surgical candidates.

## Endnotes

^a^Baseline adjustment is not relevant for the OARSI responder criteria as it incorporates baseline levels of knee pain and function into the follow-up outcome.

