#### Secondary outcomes

A range of secondary outcomes will be collected: the proportion of treatment responders using the internationally agreed Outcome Measures in Rheumatology Clinical Trials (OMERACT-OARSI) clinical responder criteria
[16,17] that combines data on pain and function from the WOMAC
[48] with patient’s global assessment of change (recorded using a 6 point Likert Scale); physical activity levels (Physical Activity Scale for the Elderly (PASE) which assesses physical activity levels over a 1-week period combining physical activity from several domains including household, occupational and leisure
[51]); self-reported body mass index (calculated from self-reported height and weight); exercise adherence (attendance at treatment sessions, self-reported adherence to prescribed exercise programme); use of local physical activity facilities in the previous 7 days (single item); a modified version of a measure of treatment acceptability and credibility
[52,53]; a measure of illness perceptions (Brief Illness Perceptions Questionnaire
[54]); confidence in ability to exercise (Self-efficacy for Exercise Scale
[55]); outcome expectations from exercise (Outcome Expectations for Exercise Scale 2
[56]); anxiety (Generalised Anxiety Disorder Assessment 7
[57]); depression (Personal Health Questionnaire Depression Scale
[58]); self-reported health care resource use (both NHS and private health care); and overall health status (EQ-5D-3 L
[59]). Resource use and EQ-5D-3 L data will be used in the cost-utility analysis (further details are provided in the ‘Economic analysis’ section).

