#### Primary and secondary trial analysis for clinical outcomes

The primary and secondary trial analysis will be conducted blind to intervention group by the statistician (EN) and an independent statistician will verify the analysis of the primary outcomes. The primary analysis will compare each of the Individually Tailored Exercise and Targeted Exercise Adherence interventions to usual physiotherapy care on an intention-to-treat basis, for the primary outcome at 6 months post-randomisation. Secondary analysis will include the analysis of the primary outcome at the secondary endpoints (3, 9, 18 and 36 months) and analysis of the secondary clinical effectiveness outcomes, as indicated in Table 
2, at all follow-up time points. Estimates of clinical effect will be derived using analysis of covariance (ANCOVA) for continuous outcome measures and logistic regression for dichotomous outcomes and will be presented as mean or percentage differences (as appropriate) with 95% confidence intervals after adjustment for baseline covariates defined *a priori* as:

• Baseline for the outcome of interest^a^

• Age

• Gender

• Duration of the knee problem

• Physiotherapy treatment centre (as was used in the randomisation algorithm)

A secondary analysis will also be completed to model the longitudinal trajectory of WOMAC pain and function over time (the primary outcome) and the PASE physical activity measure using generalized estimating equations. Model predictors will include the *a priori* covariates listed above (with the baseline for the outcome of interest modelled as a covariate rather than outcome as recommended in Peduzzi et al
[71]), time, treatment and a time*treatment interaction. A linear model will be fitted to the data (with time as a continuous measure) initially, however, if the trajectory over time is non-linear, quadratic or cubic terms will be explored. It will also be explored that conclusions do not differ if time is represented in the model as a categorical variable. All model estimates will be presented with 95% confidence intervals derived using robust standard errors.

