#### Sensitivity analysis for clinical outcomes

The following sensitivity analyses will be completed and reported if they change the interpretation of the findings from the main analysis described above.

• *Therapist effects:* these will be explored by adding a random effect term (to represent the treating therapist) to the main treatment models. The models with and without the therapist effect will be compared at each outcome time-point to explore the impact of the treating therapist on the effect estimates obtained.

• *Imputation of missing data:* a complete case analysis will be conducted and the results from this compared to those from imputed data.

• *Model covariates:* treatment models will be run on an unadjusted basis to investigate if the inclusion of model covariates has an impact on the main trial findings.

• *A per protocol analysis:* this will be completed on the subsample of participants receiving treatment in line with the specified treatment protocols. Criteria for determining the per protocol group assignment will be established by the Trial Management group and approved by the Trial Steering Committee before analysis begins.

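### Endnote a leaves baseline out of the OMERACT-OARSI responder model for a reason that does not follow, at the cost of some precision on one secondary outcome

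*Protocol article*

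**What the plan says.** Under Secondary outcomes, the protocol article lists "the proportion of treatment responders using the internationally agreed Outcome Measures in Rheumatology Clinical Trials (OMERACT-OARSI) clinical responder criteria", a measure "that combines data on pain and function from the WOMAC" with the patient's global rating of change. The thresholds are not given.

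Under Primary and secondary trial analysis for clinical outcomes, binary outcomes are to be analysed by "logistic regression for dichotomous outcomes", with results shown as percentage differences and 95% confidence intervals. The first covariate on the pre-specified list is "Baseline for the outcome of interest", followed by age, gender, duration of the knee problem and treatment centre. That first item carries endnote a, which reads: "Baseline adjustment is not relevant for the OARSI responder criteria as it incorporates baseline levels of knee pain and function". The responder model therefore keeps the other four covariates and has no baseline measure of pain or function.

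Under Sensitivity analysis for clinical outcomes, "treatment models will be run on an unadjusted basis". No run adds baseline pain or function to the responder model.

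**The concern.** The endnote treats an outcome that uses baseline in its definition as one that no longer needs baseline in its model. These are different things. People who start with high scores tend to score lower later whatever the treatment, and people who start near the bottom of a bounded scale have little room to improve. Both make the chance of being a responder vary with the starting score.

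If so, baseline pain and function are prognostic for responder status, and leaving them out gives up precision. Randomisation is stratified by clinic only, so nothing in the design balances starting severity between arms. Baseline WOMAC scores are collected before randomisation and are used in the continuous WOMAC models that will be read beside the responder result.

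The article is also not consistent on this. Under Analysis of accelerometer data, change from baseline is analysed with the same covariate list, which begins with the baseline of the outcome. There, building baseline into the outcome is not treated as a reason to leave it out of the model.

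**Working it through.** **1. The plan's own figure.** The only sample size given is for the continuous WOMAC scores: 2 × (1.960 + 0.842)² / 0.35² = 128.2, so 129 per group and 387 in all. It reproduces and is not affected by this point. Then 387 / 0.8 = 484, rounded up in the plan to 500. No figure is given for the responder outcome.

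**2. Does change depend on baseline?** Let ρ be the baseline-to-follow-up correlation and r = baseline SD / follow-up SD. Then corr(change, baseline) = (ρ − r) / √(1 + r² − 2ρr). This is zero only when ρ = r.

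| | ρ = 0.3 | ρ = 0.5 | ρ = 0.7 |
|---|---|---|---|
| r = 1.0 | −0.59 | −0.50 | −0.39 |
| r = 0.7 | −0.39 | −0.23 | 0.00 |

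The floor acts as well. On WOMAC pain (0–20), a person starting at 3 can improve by at most 3 points, which is 3/20 = 15% of the scale.

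**3. How much responder variance does baseline explain?** From the document: follow-up SD of 5/20 = 17/68 = 25% of scale. Assumed: baseline mean 42–50% and SD 18–22% of scale (r = 18/25 to 22/25, or 0.72 to 0.88), ρ from 0.3 to 0.7, and several responder rules. Each setting simulated 200,000 patients, with a logistic regression of responder status on baseline pain and function. R² is the squared correlation of fitted and observed values.

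- Absolute-change rule: 1–19%.
- Mixed rule (percentage change, absolute change and global rating): 0–13%, and 3–7% at ρ = 0.5.
- Pure percentage rule: 0–8%.

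For the mixed rule at ρ = 0.5, 24–43% responded in the lowest fifth of baseline pain and 50–64% in the highest.

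**4. What does adjustment do to power?** A separate simulation used 129 per arm, the plan's effect of 0.35 SD and an assumed composite rule. A patient responds if pain or function improves by at least 50% and by 20% of scale. A patient also responds if two of three hold: pain improved by at least 20% and 10% of scale, function likewise, and a good global rating. Also assumed: baseline means of 9 and 30, mean improvement without treatment effect of 2.5 and 8.5 points, and pain–function correlation of 0.75. There were 800 runs per setting (Monte Carlo error about 1.7 points). Responder rates below assume no treatment effect.

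| r | ρ | Responders, lowest vs highest quartile of baseline pain | Power without → with baseline |
|---|---|---|---|
| 1.0 | 0.3 | 28% vs 74% | 52% → 60% |
| 1.0 | 0.5 | 31% vs 68% | 59% → 67% |
| 1.0 | 0.7 | 34% vs 61% | 82% → 86% |
| 0.7 | 0.3 | 40% vs 65% | 63% → 66% |
| 0.7 | 0.5 | 46% vs 58% | 72% → 72% |
| 0.7 | 0.7 | 54% vs 48% | 87% → 87% |

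Type I error was near 5% with and without adjustment. In the last row ρ = r, so the linear dependence in step 2 vanishes, and so does the gain.

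**5. In patients.** The plan expects 500 × 0.8 = 400 analysed in three arms. Each contrast sets one intervention against usual care, so it uses 400 × 2/3 ≈ 267. Then 3% × 267 ≈ 8 and 7% × 267 ≈ 19. This reads R² as a variance reduction for the percentage difference. It is an upper guide, because the simulated models did not contain age, gender, duration or centre.

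**The case against.** The fairest reading of the endnote is narrow. Responder status has no baseline value of its own: it includes a global rating of change, first collected at 3 months. The note may mean only that the first covariate on the list has no counterpart for this outcome. That much is true, but it is not the reason given. The stated reason is that baseline is already built in, and that does not justify leaving out baseline pain and function, which do exist.

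Three further objections stand:

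- The analysis is valid as planned. A reader might infer bias or a wrong error rate. Randomisation rules that out, and the simulated type I error agrees. Confidence intervals already allow for chance imbalance.
- The gain rests on assumptions and may be nil. The largest gains come from equal baseline and follow-up SDs. Two of the three recruitment routes require Chronic Pain Grade 2 to 4, so a smaller baseline SD is plausible, and at r = 0.7 the gains were 0 to 3 points.
- A reader might infer that the responder outcome is the only one without baseline adjustment. It is not: exercise adherence and treatment credibility are secondary outcomes first collected at 3 months, and adherence is reported descriptively.

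Nor do the documents support the idea that a difference between the responder and WOMAC results could be put down to this omission. A dichotomised composite with a global rating can differ from a mean score for many reasons.

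**Conclusion.** The concern holds as a low-severity point about precision. The reason in endnote a is wrong as a general statement, because change-based responder status is free of baseline only in special cases. The primary WOMAC analyses are untouched.

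The size runs from about zero to modest. Applying 3–7% to all 400 analysed patients would give 12–28, but no planned contrast uses all three arms, so the two-arm range in step 5 is the one to quote. Responder thresholds, baseline means and SDs, correlations and the behaviour of the global rating are all assumed. No simulated setting showed a loss of power beyond simulation error, so the change is worth making even though the benefit cannot be fixed from the documents.

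**What to change.** Delete endnote a. State that the responder logistic model adjusts for baseline WOMAC pain and baseline WOMAC function, together with age, gender, duration of the knee problem and treatment centre.

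State also that the percentage difference and its confidence interval will be obtained by standardising the model's predictions over the trial sample. Adding covariates to a logistic model makes the odds ratio conditional on them. In the setting r = 1.0, ρ = 0.5, the mean log odds ratio moved from 0.58 to 0.67 (odds ratio about 1.79 to 1.95), so the adjusted and unadjusted odds ratios should not be compared as if they estimated the same quantity.

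The cost is a change of wording and two covariates in one model. Both are already collected, and as baselines of the primary outcomes they are already within the planned imputation model. The planned unadjusted sensitivity run can stay as it is.

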## Abbreviations

ABC knee: Attitudes and behaviours concerning knee pain; ANCOVA: Analysis of covariance; APEX: Acupuncture, Physiotherapy and Exercise; BEEP: Benefits of Effective Exercise for Knee Pain; BNF: British National Formulary; CEAC: Cost-Effectiveness Acceptability Curve; CONSORT: Consolidated Standards of Reporting Trials; CTU: Clinical Trials Unit; DNA: Treatment Non-attendance; DMC: Data Monitoring Committee; GP: General Practitioner; ICC: Intra-class correlation; ITE: Individually Tailored Exercise; NHS: National Health Service; NICE: National Institute for Health and Clinical Excellence; NIHR: National Institute for Health and Clinical Excellence; OA: Osteoarthritis; OARSI: Osteoarthritis Research Society International; OMERACT: Outcome Measures in Rheumatology Clinical Trials; PASE: Physical Activity Scale for the Elderly; PCRN: Primary Care Research Network; PCT: Primary Care Trust; PIS: Participant information sheet; PSA: Probabilistic Sensitivity Analysis; PSS: Personal Social Services; QUALY: Quality Adjusted Life Year; RCT: Randomised Controlled Trial; REC: Research Ethics Committee; SAE: Serious Adverse Event; SMART: Specific, measurable, achievable, realistic, time-related; TEA: Targeted Exercise Adherence; TOPIK: Treatment Options for Pain in the Knee; TSC: Trials Steering Committeel; UC: Usual care; UK: United Kingdom; WOMAC: Western Ontario and McMaster Universities Index.
